**1. Background and Rationale**

Partial edentulism significantly impacts oral function, aesthetics, and quality of life. Dental implants are a standard treatment, but their success depends on the surgical technique used—freehand, pilot-drilled, or fully guided. These techniques vary in accuracy, surgical time, complications, and patient satisfaction. Limited comparative data exist on their efficacy in partially edentulous patients, particularly using standardized protocols. This randomized controlled trial (RCT) aims to compare these techniques to guide clinical practice, addressing a critical gap in evidence-based dentistry.

The study is necessary to:

- Evaluate the precision and safety of implant placement techniques.
- Assess patient-centered outcomes, such as satisfaction and postoperative recovery.
- Inform evidence-based decision-making in implant dentistry.

**2. Study Objectives**

**Primary Objective**: To compare the efficacy of freehand, pilot-drilled, and fully guided implant surgery in partially edentulous patients with respect to surgical outcomes (duration, complications), postoperative recovery (pain, swelling), implant stability, osseointegration, and patient satisfaction.

**Secondary Objectives**: To evaluate long-term implant success rates and summarize the advantages and limitations of each technique to optimize clinical protocols.

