**Key Outcomes**:

- Surgical duration (minutes).
- Implant placement accuracy (via postoperative CBCT).
- Postoperative complications (within 30 days).
- Early implant failure rates (within 6 months).
- Patient satisfaction (via validated 10-point questionnaire at 6 months).
- Implant stability (via Resonance Frequency Analysis at 3, 6, and 12 months).
- Pain and swelling (via Visual Analogue Scale on Days 1 and 3).

**Study Duration**: January 6, 2025 (recruitment start) to August 3, 2025 (final follow-up).
**Sample Size**: 90 patients (30 per group), calculated for 80% power and alpha of 0.05, assuming a medium effect size (Cohen’s d = 0.5) for implant placement accuracy, with a 10% dropout rate.

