**Statistical Analysis**:

- Descriptive statistics: Mean, SD for continuous variables; frequencies for categorical variables.
- Normality testing: Shapiro-Wilk test.
- Comparative analysis: One-way ANOVA with Tukey post hoc test for group differences.
- Subgroup analysis: Canine vs. molar implants.
- Software: SPSS (Version 23).
- Significance level: $p < 0.05$.
- Analysis will follow an intention-to-treat approach.

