**Procedure**:

1. **Patient Preparation**: Same as preoperative procedure.
2. **Scan Acquisition**:
   - Use the same FOV and parameters as the preoperative scan to ensure comparability.
   - Focus on the implant site, including surrounding bone and adjacent teeth.
3. **Image Analysis**:
   - Measure deviations in implant position (mesiodistal, buccolingual, and angular) and depth (mm) using superimposition of preoperative and postoperative images.
   - Assess osseointegration indicators (e.g., bone-implant contact) and detect complications (e.g., bone perforation).
   - Analysis will be performed by a blinded radiologist to minimize bias.

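### The trial is sized on implant placement accuracy, but no objective names accuracy; the primary objective lists seven other co-equal outcomes and no primary endpoint is designated

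*Protocol*

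**What the plan says.** **Objectives (Protocol, 2. Study Objectives).** The primary objective is to compare the efficacy of the three techniques "with respect to surgical outcomes (duration, complications), postoperative recovery (pain, swelling), implant stability, osseointegration, and patient satisfaction". That is seven outcomes with no order among them. The secondary objectives cover long-term implant success and a summary of each technique's strengths and limits. Accuracy is in neither.

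**Sizing (Protocol, 3. Study Design, Sample Size).** The total is given as "90 patients (30 per group), calculated for 80% power and alpha of 0.05". The effect behind that figure is worded as "assuming a medium effect size (Cohen’s d = 0.5) for implant placement accuracy", and one patient in ten is expected to be lost.

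**Key Outcomes (same section).** Accuracy is one of seven unranked bullets. Osseointegration, which the primary objective names, is not among them.

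**Accuracy measure (CBCT imaging protocol, 6. Postoperative CBCT Procedure, Image Analysis).** The instruction is "Measure deviations in implant position (mesiodistal, buccolingual, and angular) and depth (mm"), taken by superimposing the scans before and after surgery. That is four quantities, and none is singled out.

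**Analysis (Protocol, 6. Methodology, Statistical Analysis).** One-way ANOVA with Tukey's post hoc test, and one significance level, p < 0.05. This section gives no rule across outcomes.

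**The concern.** The sample size, the objective and the decision rule should all point to the same outcome, and here they do not. The only outcome with a power claim belongs to no stated objective, and the outcomes in the primary objective have no power claim. Because no endpoint is designated as primary, the protocol does not say which result decides whether one technique is better. A report could rest its headline on whichever of the seven outcomes reaches p < 0.05 while citing 80% power that was claimed for something else.

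The sizing target is also undefined. A standardised difference of 0.5 means something different for an angle, a depth and a horizontal offset, and the protocol does not say which it has in mind.

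**Working it through.** **1. The plan's own figure.** Inputs from the Sample Size statement: d = 0.5, 80% power, alpha 0.05, 10% dropout, 30 per arm. Sidedness is not stated, so both were tried.

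- Two-sided pairwise comparison, normal approximation: n per arm = 2(1.960 + 0.842)² / 0.5² = 62.8, so 63. With dropout 63/0.9 = 70 per arm, or 210 in total. The t-test version gives 64 evaluable per arm.
- One-sided: 50 per arm, 56 with dropout, 168 in total.
- Three-group ANOVA, reading the medium effect as f = 0.25: about 158 in total, about 176 with dropout. With f = 0.40: about 64 to 66, about 75 with dropout. With f = 0.50: about 42, about 47 with dropout.

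None of these gives 90.

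**2. Power for accuracy with the planned numbers.** Power = Φ(d√(n/2) − 1.960).

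- 30 per arm: Φ(0.5 × √15 − 1.960) = Φ(−0.024) = 49%.
- 27 per arm (30 × 0.9): Φ(0.5 × √13.5 − 1.960) = Φ(−0.123) = 45%.

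These are before any adjustment for three pairs. With alpha 0.05/3 as a rough stand-in for Tukey they fall to 32% and 29%.

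**3. Where each outcome appears.**

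| Outcome | Primary objective | Secondary objectives | Key Outcomes | Power statement |
|---|---|---|---|---|
| Accuracy | no | no | yes | yes |
| Duration | yes | no | yes | no |
| Complications | yes | no | yes | no |
| Pain | yes | no | yes | no |
| Swelling | yes | no | yes | no |
| Stability | yes | no | yes | no |
| Osseointegration | yes | no | no | no |
| Satisfaction | yes | no | yes | no |

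**4. False-positive risk across the primary objective.** Assume no true differences and one overall test per outcome at 0.05.

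- Independent outcomes: 1 − 0.95⁷ = 30.2%.
- Upper bound under any dependence: 7 × 0.05 = 35%.
- Simulated one-way ANOVAs on seven equally correlated normal outcomes, 30 per arm, 6,000 replicates: 27.5% at correlation 0.3, 24.0% at 0.5, 15.3% at 0.8.

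The correlations are assumptions; the protocol gives none.

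**5. If each time point is tested separately.** The 12-month stability reading falls after the stated final follow-up of August 3, 2025, since recruitment starts on January 6, 2025. Leaving it out, the count is duration 1, complications 1, pain 2, swelling 2, stability 2, osseointegration 1, satisfaction 1, which makes 10. Then 1 − 0.95¹⁰ = 40% under independence. With the 12-month reading it is 11 tests and 43%. Repeated scores on the same patients are correlated, so the true figures would be lower.

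**The case against.** The best defence is that the SAP is not shown. Rules across outcomes, the handling of repeated measurements and the derivation of an accuracy variable commonly sit there. This stands as far as multiplicity goes: the 30% applies only if the SAP adds nothing. It does not answer the main point. Which outcome is primary, and which one the sample size serves, are settled in the protocol, and its sections would still disagree whatever the SAP adds.

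A second defence is that promoting accuracy is only one way to reconcile the text. The Background gives patient-centred outcomes as a reason for the study alongside precision, so a primary outcome could be chosen from the stated list and the trial re-sized on it. That is a legitimate alternative. Keeping all seven as primary would be costly: with Bonferroni at 0.05/7 and d = 0.5 assumed for each, about 100 evaluable patients per arm, or 112 with dropout (336 in total).

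Some stronger readings are tempting but not supported:

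- **That a false positive is likely.** For seven outcomes the risk cannot exceed 35%. A figure above one half (54%) needs 15 independent tests, reached by adding four separate accuracy tests, implant failure and every time point. Accuracy and failure are outside the primary objective, that count leaves out osseointegration and includes the 12-month reading, and the protocol does not say that each component or time point gets its own test.
- **That the subgroup analysis multiplies every test.** The protocol mentions only canine versus molar implants. It does not say that all outcomes are repeated in both.
- **That positive and negative deviations will cancel.** The protocol does not say whether deviations are averaged with sign. This is a reason to define the measure, not a demonstrated error.

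**Conclusion.** The mismatch is real and can be checked on the page: the sizing outcome is absent from both objectives, the primary objective holds seven unranked outcomes without power statements, and no primary endpoint is designated. None of this depends on an unseen document.

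The multiplicity consequence is conditional. If the SAP adds no rule and there are no true differences, the chance of at least one false positive is about 30% for seven independent outcomes and about 15% to 28% over the correlations tried, against a nominal 5%. Separate tests at each time point would raise it to about 40% under independence.

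The 80% power claim fails even for accuracy if d = 0.5 is a pairwise difference tested two-sided: it is about 49% with 30 per arm and 45% with 27. The claim also cannot be attached to a measured variable until one of the four deviations, or a combination of them, is chosen.

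**What to change.** In the primary objective, name implant placement accuracy as the single primary outcome, as the sizing statement already implies. Define it as one prespecified measure from the postoperative CBCT, for example the unsigned three-dimensional deviation from the planned position. Test it at 0.05 with Tukey-adjusted pairs, and state that d = 0.5 refers to that measure. Move the other outcomes to secondary, either adjusted for multiplicity or reported as estimates with intervals and no confirmatory claim.

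The rewording is cheap, but it has three consequences:

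- Secondary outcomes can no longer carry the headline claim.
- The power statement must be redone. Either restate what 30 per arm can detect, or re-size: a pairwise d = 0.5 needs about 70 per arm with dropout, before any adjustment for three pairs.
- The measure needs a planned position in every arm. The postoperative CBCT section compares actual positions with preoperative plans and covers all participants. The Image Processing step of the preoperative CBCT section, however, mentions only the fully guided group when describing virtual placement and guide fabrication, and the Preoperative Assessment mentions study models for planning positions. The sponsor should confirm that freehand and pilot-drilled patients also have a preoperative digital plan.

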**3. Study Design**

This is a single-center, parallel-arm RCT involving 90 partially edentulous patients, randomly assigned to three groups (n=30 each):

1. **Freehand Implant Surgery (FHIS)**: Implants placed using clinical judgment and visual landmarks.
2. **Pilot-Drilled Implant Surgery (PDIS)**: Initial osteotomy guided by a pilot drill, verified by fluoroscopy or intraoral guides.
3. **Fully Guided Implant Surgery (FGIS)**: Implants placed using customized surgical guides based on preoperative CBCT and planning software.

**Key Outcomes**:

- Surgical duration (minutes).
- Implant placement accuracy (via postoperative CBCT).
- Postoperative complications (within 30 days).
- Early implant failure rates (within 6 months).
- Patient satisfaction (via validated 10-point questionnaire at 6 months).
- Implant stability (via Resonance Frequency Analysis at 3, 6, and 12 months).
- Pain and swelling (via Visual Analogue Scale on Days 1 and 3).

**Study Duration**: January 6, 2025 (recruitment start) to August 3, 2025 (final follow-up).
**Sample Size**: 90 patients (30 per group), calculated for 80% power and alpha of 0.05, assuming a medium effect size (Cohen’s d = 0.5) for implant placement accuracy, with a 10% dropout rate.

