**Exclusion Criteria**:

- Uncontrolled systemic diseases (e.g., uncontrolled diabetes).
- Smokers or patients with a history of non-compliance with postoperative care.
- Patients requiring bone grafting or sinus lifts.

**Recruitment Process**: Patients will be recruited from dental clinics at King Khalid University. Eligible patients will receive detailed study information and provide written informed consent. Recruitment will occur between January 6 and February 3, 2025.

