**5. Preoperative CBCT Procedure**

**Purpose**: To assess bone volume, density, and anatomical structures for implant planning. **Timing**: Performed within 2 weeks before surgery.

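### Final follow-up on 3 August 2025 makes the 12-month stability visit impossible for every patient, leaves the long-term objective unanswerable, and gives the 6-month visits no slack

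*Protocol*

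**What the plan says.** Four parts of the protocol bear on this point.

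- **Section 3, Key Outcomes.** Stability is listed as "Implant stability (via Resonance Frequency Analysis at 3, 6, and 12 months". Two other outcomes also run to 6 months: "Early implant failure rates (within 6 months" and "Patient satisfaction (via validated 10-point questionnaire at 6 months".
- **Section 3, Study Duration.** The trial runs "January 6, 2025 (recruitment start) to August 3, 2025 (final follow-up".
- **Section 4, Recruitment Process.** "Recruitment will occur between January 6 and February 3, 2025".
- **Section 2, Secondary Objectives.** "To evaluate long-term implant success rates". No time horizon is attached. Implant stability is also named in the primary objective.

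The CBCT imaging protocol (section 5) says of the planning scan: "Performed within 2 weeks before surgery". The protocol gives no interval between recruitment and surgery, no closing date for surgery, no visit windows and no extension phase.

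**The concern.** A visit schedule, a recruitment window and a study end date must agree with one another, and here they do not. A 12-month measurement is promised in a study that lasts under 7 months from first recruitment to final follow-up. If the protocol is followed as written, one of the three planned stability time points will be empty for the whole trial, and a secondary objective will have no data behind it. No analysis plan can repair that, since the visits would fall after follow-up has closed.

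The 6-month outcomes raise a smaller question: whether the patients operated on last can complete 6 months before the end date.

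**Working it through.** **Inputs.** Recruitment opens 6 January 2025 and closes 3 February 2025 (section 4). Final follow-up is 3 August 2025, stability visits are at 3, 6 and 12 months, and 90 patients are planned (section 3). The lag from recruitment to surgery is not given and is treated as an assumption below.

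**1. Can the stated end date be reproduced?** Last recruitment date + lag + longest visit:

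- Longest visit 6 months, lag 0: 3 February 2025 + 6 calendar months = 3 August 2025. This matches exactly.
- Longest visit 12 months, lag 0: 3 February 2025 + 12 months = 3 February 2026. This does not match.

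The end date is consistent with a 6-month study with same-day surgery and no visit window. It is not consistent with a 12-month study.

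**2. Longest possible follow-up.** Surgery on the first recruitment day, 6 January, to 3 August: 25 + 28 + 31 + 30 + 31 + 30 + 31 + 3 = 209 days, and 209 / 30.4375 = 6.87 months. Surgery on 3 February to 3 August: 209 − 28 = 181 days.

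**3. The 12-month visit.**

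| Surgery date | 12-month date | Days after 3 August 2025 |
|---|---|---|
| 6 January 2025 | 6 January 2026 | 156 |
| 3 February 2025 | 3 February 2026 | 184 |

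To reach 12 months by 3 August 2025, surgery would have to be by 3 August 2024, about 5 months before recruitment opens. So 0 of 90 patients can have the value. Any lag before surgery only widens the gap.

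**4. The long-term objective.** The protocol attaches the word early to failure within 6 months. The longest follow-up exceeds that by 6.87 − 6 = 0.87 months.

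**5. The 6-month visits.** The latest surgery date with a 6-month date on or before 3 August is 3 February in calendar months (2 February if 6 months is taken as 182 days, 4 February if 180). Assume recruitment is even over the 29 dates from 6 January to 3 February, and every patient has the same lag of L days, with L at most 29. The share operated on after 3 February is then L / 29:

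| Assumed lag | Share with 6-month date after study end |
|---|---|
| 0 days | 0/29 = 0% |
| 7 days | 7/29 = 24% |
| 14 days | 14/29 = 48% |
| 28 days | 28/29 = 97% |

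For the last recruit with a 14-day lag, surgery falls on 17 February. Observation to 3 August is 181 − 14 = 167 days, or 5.5 months.

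**The case against.** There is no good defence of the 12-month visit. The end date is described as final follow-up, so it does not read as an interim cut-off.

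The defence of the 6-month outcomes is stronger, and most of it stands. The dates do fit if surgery takes place within the recruitment window, and nothing in the protocol says that surgery happens later. A reader might take the two-week limit on the planning CBCT as a two-week wait after recruitment. It is not: it caps the age of the scan at surgery. Because CBCT-confirmed bone volume is an inclusion criterion (section 4), some or all of that time may pass before enrolment. The shares in the table are therefore set almost entirely by the assumed lag, and the zero-lag case belongs in the range.

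Three further readings are tempting, but the documents do not support them.

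- **That late 6-month visits would use up the 10% dropout allowance.** That allowance belongs to a sample size based on placement accuracy, which is measured on a CBCT within 1 week after surgery. Late 6-month visits do not touch it.
- **That losses would fall mainly on the fully guided arm, because its guide must be made first.** The protocol places guide fabrication before surgery but gives no duration, so the size of any imbalance is speculation.
- **That patients operated on late lose the failure outcome.** It is a window up to 6 months, so most of it would still be observed. The 6-month stability and satisfaction assessments are more exposed, though with no visit window stated a visit a few days early is not necessarily lost.

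It can also be said that long-term is undefined, so calling the objective unanswerable is an inference. That is fair, but the inference rests on the protocol's own use of the word early.

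**Conclusion.** The contradiction over the 12-month visit is certain and needs no assumption: 0 of 90 patients can have a 12-month stability value. The long-term objective falls with it, on the protocol's own vocabulary rather than on date arithmetic alone.

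The 6-month point is conditional. There is no slack: for any patient operated on after 3 February, the 6-month stability and satisfaction dates fall after study end and failure follow-up is slightly short. The documents do not show that this will happen to anyone. The range of 0% to about 48% for lags of 0 to 14 days rests on assumed even recruitment and an assumed common lag.

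Surgical duration, placement accuracy, 30-day complications, early pain and swelling, and 3-month stability are not put in doubt by any lag considered here. The 12-month contradiction and the long-term objective must be corrected; the missing slack at 6 months should be corrected in the same amendment.

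**What to change.** Reconcile the dates with the visits, and state that every visit is counted from the date of surgery. There are two coherent ways to do it.

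**(a) A 6-month study.** Delete the 12-month stability measurement. Remove the long-term objective, or limit it to the 6-month failure outcome already listed, and claim nothing beyond 6 months. Define study end as the last surgery plus 6 months plus a stated visit window. With an assumed 14-day lag for the last recruit, that means 17 August 2025 plus the window. The cost is a few weeks at the end and no long-term claim.

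**(b) A 12-month study.** Keep the 12-month visit and move final follow-up to at least 12 months after the last surgery: 3 February 2026 at zero lag, or 17 February 2026 with an assumed 14-day lag, plus the window. The cost is about 6 to 7 more months of follow-up. The long-term objective would still need a stated horizon, which could then be 12 months.

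Under either option, state the period in which surgery will take place, so that the end date can be checked against it.

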**6. Methodology**

**Randomization**: Computer-generated randomization (1:1:1 ratio), stratified by age and gender, will assign participants to FHIS, PDIS, or FGIS groups.

**Blinding**: Surgeons and participants cannot be blinded due to the nature of the interventions. Outcome assessors (radiologists, statisticians) will be blinded to group allocation to reduce bias.

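### Thirty patients per group give about 30% to 49% power at Cohen's d = 0.5, not the stated 80%

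*Protocol*

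**What the plan says.** The Protocol describes a parallel trial with patients "randomly assigned to three groups (n=30 each") and 1:1:1 allocation (sections 3 and 6). Its only sample-size justification is under Key Outcomes in section 3, for 90 patients: "30 per group), calculated for 80% power and alpha of 0.05, assuming a medium effect size", stated as Cohen's "d = 0.5) for implant placement accuracy, with a 10% dropout rate".

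The test is fixed in section 6, Statistical Analysis: "Comparative analysis: One-way ANOVA with Tukey post hoc test for group differences". The Protocol does not give the formula used, the sidedness, a standard deviation, the pattern of the three means, or the pair of groups to which d applies.

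**The concern.** A two-group comparison at d = 0.5 with 80% power is a familiar calculation that gives just over 60 patients per group. Thirty per group, less 10% dropout, is under half of that, and a three-group Tukey procedure needs more patients, not fewer.

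This is the trial's only power statement, and it justifies enrolling 90 people for surgery and two CBCT scans each. If power is really a third to a half, a true medium difference in accuracy between techniques is more likely to be missed than found. A reader who trusts the 80% would then give a non-significant result more weight than it can bear. That last step is an inference about readers; the Protocol does not claim equivalence.

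**Working it through.** **Inputs.** From section 3: alpha 0.05, target power 80%, d = 0.5 (so SD = 1), 30 per group, 10% dropout, hence 30 × 0.9 = 27 evaluable per group. From sections 3 and 6: three independent groups, one-way ANOVA, then Tukey. Assumed: two-sided testing and one accuracy value per patient.

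**Attempt to reproduce 30 per group.** By the normal approximation,

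n = 2(1.960 + 0.842)² / 0.5² = 62.8, so 63 per group.

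The exact t calculation gives 63.8, so 64; with dropout, 64 / 0.9 = 71.1, so 72. The stated 30 is not reproduced.

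**Power, unadjusted pair.** The noncentrality is 0.5 × √(n/2): 1.837 at n = 27 and 1.936 at n = 30. Against t critical values of 2.007 (52 df) and 2.002 (58 df), power is 43.8% and 47.8%.

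**Power, Tukey pair.** The noncentrality is the same. The critical value is q(0.95; 3 groups, 3n − 3 df)/√2: 2.389 at n = 27 and 2.384 at n = 30. Power is 29.6% and 33.2%.

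**Power, omnibus F.** f is the SD of the three means divided by the common SD. If the largest difference is 0.5 SD, f lies between two cases:
- third group midway: f = √[(0.25² + 0 + 0.25²)/3] = 0.204
- one group different, two equal: f = √[(2 × (1/6)² + (1/3)²)/3] = 0.236

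With noncentrality N·f² (3.375 and 4.5 at N = 81; 3.75 and 5.0 at N = 90), power is 34.5% and 44.5% at N = 81, and 38.1% and 48.9% at N = 90.

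| Reading of d = 0.5 | Power, 27 per group | Power, 30 per group | Evaluable per group for 80% | Per group after dropout (total) |
|---|---|---|---|---|
| Unadjusted pair | 43.8% | 47.8% | 64 | 72 (216) |
| Tukey pair | 29.6% | 33.2% | 83 | 93 (279) |
| ANOVA, third group midway | 34.5% | 38.1% | 79 | 88 (264) |
| ANOVA, one group different | 44.5% | 48.9% | 59 | 66 (198) |

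**Other readings.**

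| Reading | Power, 27 per group | Power, 30 per group | Per group after dropout |
|---|---|---|---|
| One-sided unadjusted pair | 56.7% | 60.6% | 57 |
| Medium taken as f = 0.25 | 49.3% | 54.0% | 59 |
| Steps of 0.5 SD between successive groups (f = 0.408) | 90.8% | 93.6% | 24 |
| d entered as f = 0.5 | 98.3% | 99.1% | 16 |

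None gives 30. One calculation does: a one-sided paired or one-sample t test at d = 0.5 needs 27, and 27 / 0.9 = 30. It does not apply to three parallel groups, though it may be how the figure arose.

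**What 27 per group can detect with 80% power.** d = 0.78 for an unadjusted pair, d = 0.88 for a Tukey pair, f = 0.35 for the omnibus test. The 95% Tukey interval for a pairwise difference has half-width 2.389 × √(2/27) = 0.65 SD, wider than the 0.5 SD the trial says it is sized for.

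**The case against.** The best case for the plan has five parts.

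- **Dropout hardly touches this endpoint.** Accuracy is read from a CBCT taken within a week of surgery, so the figures at n = 30 may be the fairer ones. This stands, but they still reach only 33% to 49%.
- **The effect pattern and sidedness are not defined.** Under f = 0.25 at n = 30, or a one-sided test, power is 54% to 61%, and a medium effect would then be found slightly more often than missed. That limits the wording of the consequence. However, the Protocol states d, not f, and Tukey's procedure is two-sided. The stepwise pattern would give ample power, but the Protocol does not state it and it leads to 24 per group.
- **Patients may receive more than one implant.** If each had two, with an assumed intraclass correlation of 0.2 to 0.5, the effective number per group would be 60/1.2 = 50 down to 60/1.5 = 40. Power would be about 60% to 70% for an unadjusted pair and 45% to 55% under Tukey: better, but short of 80%. The Protocol gives neither figure and counts patients.
- **Nothing says that a null result will be read as equality.** True; that is a risk, not a stated intention.
- **Interval reporting may be in an SAP that is not shown.** Also true. But no SAP can make the Protocol's own power figure correct.

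**Conclusion.** The concern holds. The stated 80% power does not follow from the stated inputs under any standard method for three independent groups. On the two-sided readings of d = 0.5, power is about 30% to 49%; on the planned Tukey comparison it is 30% to 33%. Eighty per cent would take 198 to 279 randomised patients instead of 90, a two- to three-fold shortfall that rounding cannot explain.

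This rests on two-sided testing at 5%, one accuracy value per patient, equal SDs, and d = 0.5 as the largest difference between any two groups. Relaxing sidedness, or reading the effect as f = 0.25, raises power to at most 61%. Only a larger effect than the Protocol states, such as 0.5 SD at each step, brings it above 80%, and that does not reproduce 30 per group either.

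**What to change.** Keep 90 patients and replace the sample-size statement in section 3 with one the design supports, for example:

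> With 27 evaluable patients per group (30 randomised, 10% dropout), the trial has 80% power at two-sided alpha 0.05 to detect a difference of 0.88 SD in placement accuracy between any two groups with Tukey adjustment, or f = 0.35 in the overall ANOVA. Power for a difference of 0.5 SD is about 30% per pair.

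The same paragraph should state the comparison, the sidedness and the unit of analysis (patient or implant). It should also say whether a difference of 0.88 SD would matter in practice: that value is solved back from the fixed sample size and is not in itself a justification for it.

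In section 6, or in the SAP if it is not already there, commit to reporting each pairwise difference with its 95% Tukey interval, and state that a non-significant result is not evidence of equal accuracy.

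The cost is rewording and a less favourable power statement; no patients, visits or scans are added. Keeping the claim of 80% power at d = 0.5 with Tukey would instead require 93 patients per group, 279 in all.
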